#### Analysis of the secondary endpoint(s)

Analysis of secondary outcomes that are continuous such as out-of-pocket expenditure will follow the same analytic approach outlined for the primary outcomes. For binary outcomes, such as initiation of treatment, use of financial services (yes/no), or account delinquency, we will use modified Poisson regression models. Models will use a log link function estimated with GEE, with an independent working correlation structure and robust covariance estimation, and will account for clustering by oncology department. Intervention effects will be presented as the relative risk of the outcome in each of the intervention groups relative to Usual Care, with 95% confidence intervals.

To assess the short-term impact of financial navigation on health service use and treatment outcomes, we will conduct analysis of several secondary outcomes at 3 months. These include (1) medical financial assistance (MFA) application (yes/no) [Secondary: MFA application approved or denied; type of MFA award received] and (2) initiation of treatment (yes/no) [Secondary: time-to-initiation of treatment; type of treatment]. Assessment of 3-month outcomes will follow the general approach outlined for 12-month primary and secondary outcomes, except that the intervention group will be a binary variable. Group 2 (Brief intervention) and Group 3 (Extended intervention) participants will be combined for analysis, and effect estimates will compare this combined intervention group to usual care.

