### Eligibility criteria {10}

Inclusion criteria:KPNW and KPWA members with a new cancer diagnosis (within the past 120 days from identification date)18+ years of age (based on age at time of identification date by the study eligibility program)Visit to CAFÉ clinic/department within two weeks of identification dateCurrent, living member as of identification dateContinuous enrollment at least 6 months prior to identification dateEnglish speaker for KPWA; English or Spanish speaker for KPNW

Exclusion criteria:On do-not contact or no chart review listCancer diagnosis is for non-melanoma skin cancerCancer diagnosis is for a benign or in situ tumorHospice encounter in past yearSelf or household member has already enrolled or completed participation in CAFÉ pilot study or main trial.Unable to complete survey

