**Secondary**		
2. Compare health service use between patients receiving the CAFÉ intervention versus a comparison group at 12-month follow-up.	Survey: Material, behavioral, and psychological financial hardship Medical Expenditure Panel Survey (MEPS) items [43] Global quality of life PROMIS Global health [44–47] Patient-centered communication: Patient Assessment of cancer Communication Experiences (PACE) [48] (EHR) Delayed or foregone care assessed by treatment initiation^a^ and time to treatment initiation^a^ Use of KP medical financial assistance services^a^; total out-of-pocket expenditure; account delinquency	The CAFÉ intervention could facilitate early identification of patient affordability concerns and care plan adjustments; improve access to financial planning resources or payment plans; and by connection to referrals and resources for acute financial distress.
3. Assess patient-level factors influencing variability in dose of the CAFÉ intervention.	Intervention dose received (Arm 2 vs Arm 3)	Estimation of ideal dose will be important for future implementation of the intervention.

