### Sample size {14}

The study will enroll 185 participants at each site (total *n*=370; approximately 123 per randomization group). Primary outcome measures for Objective 1, are assessed via survey at 12 months. Assuming 20% attrition, the analytic sample size for Aim 1 outcomes will be 296 patients (*n*=99 per group). With a type 1 error rate of 0.05 (two-sided), we will have 80% power to detect effect sizes of Cohen’s *d* = 0.40 for continuous outcomes. For the primary outcome of financial distress, this translates to a least detectable difference of 0.96 on the InCharge financial distress scale (10-point measure) for pairwise comparisons between randomization groups, assuming a standard deviation of 2.4 [41]. For the binary financial hardship measures (secondary outcomes), the least detectable difference depends on the proportion reporting financial hardship in the comparison group. We have 80% power to detect at 17.4% difference in financial hardship if the reported rate is 35% in the comparison group, corresponding to a rate of 17.6% among intervention patients (pairwise comparison of randomization groups). If the rate among comparison patients is much lower at 15%, the least detectable difference is 11.4%.

Based on our estimated sample size and a standard deviation of 5.0 as reported in the measure development work establishing the validity and reliability of the FACT-G7 in ambulatory cancer patient population [42], we estimate that we will be able to detect a 2.0-point difference in health-related quality of life (HR-QOL) between intervention and control groups. Since a 2 to 3 point difference on the FACT-G7 is considered clinically meaningful [42], we will be able to detect clinically meaningful changes on the FACT-G7 during the CAFÉ study.

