### Methods in analysis to handle protocol non-adherence and any statistical methods to handle missing data {20c}

The investigators and data managers will monitor data collection process on a weekly basis and ensure a minimal amount of loss to follow-up in the study. All analyses will be conducted following a modified intent-to-treat approach, including all individuals randomized regardless of their engagement with, or exposure to the intervention. Individuals with missing outcome data will not be included in the primary analysis. We will conduct an analysis assessing factors related to missing outcome assessment. We will fit logistic regression models with missing primary outcome (yes/no) as the binary outcome in the logistic regression model, and baseline characteristic variables as independent variables, to determine predictors for missingness. Baseline covariates that are significantly (at 0.10 significance level) associated with missingness from this model will be adjusted in all models to ensure the validity of a missing-at-random (MAR) assumption. If loss to follow-up is above 15%, we will employ appropriate statistical techniques to address missing data issues. We will consider multiple-imputation analyses, or inverse probability weighting to account for missingness.

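### Time to treatment initiation is assigned to models that cannot handle participants who have not started treatment

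*Protocol article*

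**What the plan says.** Table 1 of the protocol article gives, among the EHR secondary endpoints, "Delayed or foregone care assessed by treatment initiation" together with time to treatment initiation. Its footnote has both assessed at 3 and 12 months.

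Under Analysis of the secondary endpoint(s), initiation (yes/no) is a 3-month outcome, with "time-to-initiation of treatment; type of treatment" in brackets as further outcomes beneath it. The model is then assigned by reference: "Assessment of 3-month outcomes will follow the general approach outlined for 12-month primary and secondary outcomes". The one exception stated is that Arms 2 and 3 are pooled and compared with usual care.

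The approach referred to has two parts:
- Continuous outcomes: linear regression by GEE, reported as differences in group means.
- Binary outcomes, with initiation named as an example: modified Poisson regression, reported as relative risks.

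Three other sections bear on the point:
- Section {11b} stops EHR data flow when a participant withdraws.
- Section {20c} says: "Individuals with missing outcome data will not be included in the primary analysis".
- Eligibility {10} admits members with a "new cancer diagnosis (within the past 120 days from identification date" and a visit to a study clinic within two weeks of that date. It has no criterion on treatment already begun. Recruitment {15} adds that the visit is an initial one after diagnosis.

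**The concern.** A time is not a binary outcome, so the assignment as written points to a difference in means. A mean needs a value for everyone. A participant who has not started by the end of the window has none, and one whose records stop at withdrawal, disenrolment or death has only a lower bound. The article names no model that can use such partial information. The practical result is a mean over those who started.

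Whether someone starts is what navigation is meant to change. Comparing arms among starters therefore conditions on a consequence of treatment, and randomisation no longer protects the comparison. The participants lost are those who forwent care, half of what the endpoint is meant to capture. The yes/no and time results could then point in opposite directions.

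A second, smaller issue is the starting point. Someone who began treatment between diagnosis and randomisation cannot have initiation affected by navigation, whose first visit is at Day 10 (Table 2).

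**Working it through.** **The plan's own figure.** The article gives no power or sample size for time to initiation. Its stated calculation is for the primary outcomes: "With a type 1 error rate of 0.05 (two-sided), we will have 80% power to detect effect sizes of Cohen’s" d = 0.40, with 99 analysed per group. This reproduces: 2 × (1.960 + 0.842)² / 0.40² = 98.1, rounded up to 99, with power 80.4%. Only the enrolled number is used below: "370; approximately 123 per randomization group", so about 123 v 247 once Arms 2 and 3 are pooled.

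**Assumptions.** The documents give no start rates or start times. All such inputs below are illustrative. The window is 90 days. Two summaries are compared: the mean start day among starters, and the restricted mean time to day 90, in which a non-starter contributes 90 days. Negative means earlier with navigation.

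**Case A: everyone's rate of starting rises (proportional hazards).** With exponential times, λ0 = −ln(1 − p0)/90 and λ1 = HR × λ0. The starters' mean is 1/λ − 90e^(−90λ)/(1 − e^(−90λ)). The restricted mean is (1 − e^(−90λ))/λ.

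Worked example, p0 = 70%, HR = 1.2: λ0 = 0.01338 and λ1 = 0.01605.
- Starters' mean: 34.5 v 36.2 days, difference -1.7.
- Restricted mean: 47.6 v 52.3 days, difference -4.7.

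Over p0 = 60–90% and HR = 1.2–1.5, the starters-only difference is -1.3 to -6.0 days and the restricted-mean difference is -4.3 to -10.8 days. The sign is kept and the effect shrinks.

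**Case B: navigation adds late starters and changes nobody else.** Control: 70% start, mean day 30. Intervention: the same 70%, plus 10% who start at mean day 75.
- Starters' mean: (0.70 × 30 + 0.10 × 75)/0.80 = 28.5/0.80 = 35.6 days, v 30. Difference +5.6.
- Restricted mean: 0.70 × 30 + 0.10 × 75 + 0.20 × 90 = 46.5 days, v 0.70 × 30 + 0.30 × 90 = 48.0. Difference -1.5.

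Over control start rates of 70–90%, 5–10% extra starters and extra-starter means of day 50–75, the starters-only difference is +1.1 to +5.6 days while the restricted mean improves by 0.8 to 4.0 days. The sign reverses.

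**Case C: as B, but everyone else also starts 2 days earlier.** The starters-only difference runs from -0.8 to +3.9 days, so either sign is possible.

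**Treatment before randomisation.** Let a share q have started already in every arm, with 70% v 80% starting among the rest. The observed rates are q + (1 − q) × 0.70 and q + (1 − q) × 0.80, so the 10-point difference becomes 10 × (1 − q). Power is for a simple two-proportion test, 123 v 247.

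| q (assumed) | Rates | Relative risk | Power, all participants | Power, untreated only |
|---|---|---|---|---|
| 0 | 70.0% v 80.0% | 1.14 | 57% | 57% |
| 25% | 77.5% v 85.0% | 1.10 | 44% | 46% |
| 50% | 85.0% v 90.0% | 1.06 | 30% | 33% |
| 75% | 92.5% v 95.0% | 1.03 | 18% | 20% |

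The last column keeps 70% v 80% and multiplies both group sizes by (1 − q). Restricting to untreated participants restores the size of the effect but recovers little power.

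**The case against.** The strongest reply is that the reference to a general approach is loose wording in a journal article. The same bracketed lists include type of treatment and type of assistance award, which fit neither model, so the sentence may be a summary rather than a full assignment. An analysis plan not shown here could name a survival model. That lowers the certainty. It does not remove the point, because the article assigns this outcome to a set of models with none for censored times and states a single exception that concerns something else.

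Three further replies stand:
- A reader might infer from section {20c} that non-starters are expressly excluded. They are not. The rule concerns missing outcome data in the primary analysis, and a person whose record shows no start has an observed yes/no result. That starters alone would enter a mean is a practical consequence, not a stated rule. The imputation or weighting that section offers above 15% loss does not solve it, since an observed period without a start is not a missing value.
- The paired yes/no outcome would still show the gain (80% v 70% in Case B), so a misleading mean would not stand alone.
- The initial-visit wording in Recruitment {15} limits how many participants were already treated. Eligibility {10} still leaves room for them, but their share is unknown.

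**Conclusion.** The point holds for one secondary outcome. Followed as written, time to initiation is analysed by a difference in means with no valid value for non-starters or for follow-up that ends early. Under the assumed scenarios this shrinks the effect when navigation speeds up starting generally (Case A), and can reverse it when navigation mainly brings in late starters (Case B). The direction depends on inputs that the documents do not give.

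A reader might go further and conclude that the plan will turn a benefit into a delay. The documents do not support that, since reversal needs a particular pattern of effect and touches only the time component. Nor do they call delayed care the main health-service outcome of Aim 2: Table 1 also lists use of financial assistance, out-of-pocket expenditure and account delinquency. Prior treatment is a separate, secondary matter. It dilutes both initiation outcomes by the factor (1 − q), with q unknown, and does not cause reversal.

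The primary outcomes and their sample size are unaffected.

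**What to change.** State a censoring-aware analysis for time to treatment initiation:
- Measure time from randomisation to first cancer treatment.
- Report cumulative incidence by arm, with a Cox model or restricted mean time, and variance robust to clustering by oncology department.
- Treat death as a competing event, and censor at withdrawal, disenrolment or the end of the 3- or 12-month window.
- Report the result beside initiation yes/no, so that how many start and how soon are read together.

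Also analyse both initiation outcomes in participants with no cancer treatment recorded before the randomisation date, and report the number excluded by arm. This subset is defined by baseline data, so the randomised comparison is preserved within it.

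The cost is analysis wording and the use of EHR treatment dates, which the outcome needs in any case. The drawback is fewer participants for this secondary outcome. If the full analysis plan already specifies such a method, a cross-reference is enough.

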### Interim analyses {21b}

No interim analyses are planned.

### Methods for additional analyses (e.g., subgroup analyses) {20b}

#### Mixed methods analysis: patient-level factors associated with intervention dose received

The optimal dose of financial navigation needed to impact financial hardship and health-related quality of life is not well understood and has substantial implications for future implementation of financial navigation interventions. By design, intervention participants (Arms 2 and 3) can initiate contact with CAFÉ navigators any time during the 6-month intervention period, and so can receive additional navigation services beyond the minimum specified in the protocol. We therefore expect that the total dose received of the CAFÉ intervention to vary between participants based on individual needs; thus, our third study aim involves mixed methods analyses of patient-level factors associated with the intervention dose received.

Our conceptual definition of dose includes several components: the total quantity of financial navigation cycles offered and received; participant engagement/participation in the intervention; and appropriateness of the CAFÉ intervention for addressing participant financial questions and concerns. Further, we distinguish conceptually between the intervention dose offered per the protocol and dose received: the total number of navigation cycles that each intervention participant receives (Table 3).

**Table 3 Tab3:** CAFÉ study dose-related constructs

Construct	Definition
Dose offered (aka adherence per protocol)	- One financial navigation cycle over 6 months (Arm 2 brief intervention participants) - Three financial navigation cycles over 6 months (Arm 3 extended intervention participants)
Navigation cycle	One financial assessment visit between navigator and participant plus associated follow-up until concern is addressed
Ad hoc cycle	Financial navigation cycle initiated outside of protocol cycles (spontaneous contact initiated by participant, family member, or clinical team) to disclose a new concern
Total dose received	Total number of navigation cycles completed by the participant (protocol cycles plus extra cycles)
Cycle initiator	Whether intervention cycle was per protocol; participant-initiated; or clinician-initiated
Navigation pathway	Concerns addressed in each intervention cycle (acute financial needs; planning/budgeting for future expenses; need for cost information to inform clinical decision-making; or low touch)

We plan three quantitative analyses related to dose (a) intervention effects of the randomized dose offered, (b) predictors of high versus low dose received, and (c) differences in study outcomes controlling for dose received. We will conduct descriptive and multivariable analyses for each of these analyses, including sociodemographic and other covariates as well as characteristics of the intervention cycles (e.g., cycle initiator and financial concerns pathways).

Qualitative analyses will include thematic content analysis of navigator notes from the study REDCap database, including the four brief questions about the participant’s experience with the intervention asked at the final closure contact. Analysts will conduct qualitative content analysis, with the goal of providing insight into participant engagement with the intervention, as well as reports of the appropriateness or fit of the intervention with participant needs.

Our mixed methods approach will use a sequential explanatory design with triangulation protocol [44, 45]. We will collect quantitative and qualitative data relatively independently but iteratively where appropriate, with a series of triangulation analysis meetings to discuss convergence, complementarity, and discrepancy of findings. For example, if quantitative analysis identifies a specific group of participants with a very high intervention dose received; qualitative analysts might conduct a focused analysis to explore the fit of the intervention for that group.

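### Objective 3, analysis (b): a single total of scheduled plus ad hoc cycles would, if split high/low across Arms 2 and 3, largely sort patients by arm and attendance, and cycle initiator cannot serve as a predictor of it

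*Protocol article*

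**What the plan says.** Objective 3 is to assess patient-level factors behind variability in dose. The section on mixed methods analysis of dose received explains why dose should vary: participants in both intervention arms may contact the navigator themselves, so total dose is expected to follow individual need.

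Table 3 fixes the terms:
- Dose offered is "One financial navigation cycle over 6 months (Arm 2 brief intervention participants") and "Three financial navigation cycles over 6 months (Arm 3 extended intervention participants").
- A cycle is "One financial assessment visit between navigator and participant plus associated follow-up until concern is addressed".
- An ad hoc cycle is a "Financial navigation cycle initiated outside of protocol cycles (spontaneous contact initiated by participant, family member, or clinical team) to disclose a new concern".
- The total dose received is "Total number of navigation cycles completed by the participant (protocol cycles plus extra cycles").
- Cycle initiator has three values: per protocol, participant or clinician.

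The same section plans three quantitative analyses. The second is ("b) predictors of high versus low dose received". All three are to use descriptive and multivariable methods, "including sociodemographic and other covariates as well as characteristics of the intervention cycles (e.g., cycle initiator and financial concerns pathways"). It gives no cut-off for high dose and does not say how randomised arm enters. Table 1 labels the endpoint as dose received, Arm 2 versus Arm 3.

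**The concern.** The total adds two different quantities. Scheduled cycles are capped by randomisation at 1 or 3, and below that cap they depend on the navigator reaching the patient (up to six call attempts per visit, under strategies to improve adherence). Ad hoc cycles arise when someone raises a new concern, and these are the cycles the section's own rationale relies on.

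An Arm 3 patient who takes three low-touch scheduled visits scores 3. An Arm 2 patient who attends the one scheduled visit needs two new ad hoc cycles to score the same. A high/low split of that total across both arms would mostly return the allocation, and associations with patient characteristics would look weaker than they are.

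Cycle initiator raises a separate problem. It describes the components of the total, so it cannot also explain the total.

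Table 1 justifies this objective by the need to estimate an ideal dose for implementation. The qualitative work may also be directed at a very-high-dose group, which could be chosen largely by arm.

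**Working it through.** **Plan's own figure.** There is none for Objective 3. The article's sample-size calculation concerns Aim 1 and has no bearing here. From the documents: offers of 1 and 3 cycles, 1:1 allocation between Arms 2 and 3, and about 123 patients per arm (246 in the two).

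**Limiting case, no assumptions on rates.** With full attendance and no ad hoc cycles, dose is exactly 1 or 3, and arm explains 100% of its variance.

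**Circularity, no simulation.** In Arm 2, at most one cycle can be per protocol. A dose of 2 or more therefore implies at least one cycle whose initiator is participant or clinician. The predictor is contained in the outcome.

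**First model (assumptions, not in the documents).** The probability of attending a scheduled visit varies between people as a beta distribution with mean *p* and a + b = 4. Ad hoc cycles are Poisson with gamma-distributed need (shape 1) and mean *m*, so their variance is m + m². Attendance is unrelated to need.

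Worked case, p = 0.7, m = 0.3:
- Ad hoc: P(0) = 1/1.3 = 0.769; P(1) = 0.769 × 0.3/1.3 = 0.178.
- Arm 2: P(dose 0) = 0.3 × 0.769 = 0.231; P(dose 1) = 0.7 × 0.769 + 0.3 × 0.178 = 0.592; P(dose ≥ 2) = 0.18.
- Arm 3 scheduled cycles (beta-binomial, a = 2.8, b = 1.2): P(0, 1, 2, 3) = 0.070, 0.185, 0.319, 0.426. P(dose 0) = 0.054; P(dose 1) = 0.155; P(dose ≥ 2) = 0.79.
- Arm 3 share of the high group = 0.79/(0.79 + 0.18) = about 82%.
- High-dose patients with no ad hoc cycle = (0.319 + 0.426) × 0.769/(0.791 + 0.178) = 59%.
- Variance: between arms (2 × 0.7)²/4 = 0.49; scheduled cycles within arm, averaged, (0.21 + 0.882)/2 = 0.546; ad hoc 0.3 + 0.09 = 0.39; total 1.426. Scheduled cycles carry 1.036/1.426 = 73%, and arm alone 34%.

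Across p = 0.5, 0.7 and 0.9 (simulated):

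| Mean ad hoc cycles | Variance from scheduled cycles | Variance from arm alone | Arm 3 share of ≥ 2 group | Correlation with need: total dose pooled / ad hoc only |
|---|---|---|---|---|
| 0.1 | 89–91% | 25–70% | 91–92% | about 0.09 / 0.30 |
| 0.3 | 70–73% | 19–56% | 80–82% | about 0.26 / 0.48 |
| 0.5 | 55–58% | 15–45% | 74–75% | about 0.38 / 0.58 |
| 1.0 | 31–34% | 9–27% | 65–67% | about 0.58 / 0.71 |

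**Second model (also assumed).** Attendance is 85% for the first and 70% for later visits. The ad hoc rate doubles per SD of need, with mean 0.38 in Arm 2 and half that in Arm 3. With high dose set at 2 or more cycles, 26% of Arm 2 and 87% of Arm 3 are high, so Arm 3 makes up 87/(87 + 26) = 77% of the group. Odds ratios for need per SD:

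| Outcome | Attendance vs need | Arm 2 | Arm 3 | Pooled, no arm term | Arm-adjusted |
|---|---|---|---|---|---|
| ≥ 2 cycles | unrelated | 2.3 | 1.1 | 1.4 | 1.7 |
| ≥ 2 cycles | odds × 1.5 per SD | 2.5 | 2.1 | 1.7 | 2.3 |
| Any ad hoc cycle | unrelated | 2.4 | 2.2 | – | 2.3 |

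The last row recovers the need effect partly by construction, because in that run only ad hoc cycles were made to depend on need.

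At these rates about 36 of 123 patients in Arm 2 and 20 of 123 in Arm 3 would have any ad hoc cycle (56 of 246).

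**The case against.** **Pooling is not stated.** The article gives no cut-off, does not exclude arm from the model, and labels the endpoint by arm in Table 1. An analysis plan could stratify. It could also define high dose as more than the number of cycles offered; under the second model with attendance unrelated to need, that gives odds ratios of 2.3 in Arm 2, 2.2 in Arm 3 and 2.1 pooled. This stands, and it makes the arm-sorting point conditional. The circularity point does not depend on it.

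**Attendance is part of the construct.** The conceptual definition of dose includes engagement and participation, so answering scheduled calls is not noise. This stands as a reason to report attendance. It is not a reason to add it to ad hoc use in one score.

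**Cycle initiator might be used only descriptively.** The article speaks of descriptive and multivariable analyses, so that is possible. But initiator is listed among the covariates for each dose analysis, and its role in analysis (b) needs stating.

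**Two stronger readings are tempting and are not supported.** A reader might infer that adjusting for arm cannot help. The second model shows that this depends on attendance being unrelated to need, which no section establishes; when need raises attendance, adjustment recovers 2.3. A reader might also infer that counting completed cycles penalises patients with hard, unresolved concerns. The navigator decides when a cycle ends, there is a closure contact at six months, and nothing says an open cycle goes uncounted.

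**Conclusion.** The point holds in a limited form. The definition of dose received combines an allocation-driven part and a need-driven part, and a single high/low split over Arms 2 and 3 would largely reflect arm and scheduled attendance. Arm 3 forms 65–92% of a two-or-more-cycles group in every scenario of the first model, and 77% in the second. Scheduled cycles account for most of the dose variance up to about 0.5 ad hoc cycles per person, but not at about 1 per person.

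Because arm is randomised, the effect is dilution of patient-level associations, not confounding. How large it is rests on ad hoc uptake and on the link between need and attendance, neither of which the documents give.

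Using cycle initiator to predict dose is circular by Table 3's own definitions, whatever those rates are.

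Severity is minor to moderate. Table 1 lists the objective under secondary endpoints, but the abstract calls the analysis exploratory. The primary outcomes and the comparison of randomised dose offered are untouched.

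**What to change.** In analysis (b), replace the single total with two outcomes:
- **Scheduled uptake:** the share of offered scheduled visits held (of 1 in Arm 2, of 3 in Arm 3), reported by arm.
- **Ad hoc use:** any ad hoc cycle, and the number, modelled with an arm term and, as a check, within arm.

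Use only baseline patient factors as predictors. Describe cycle initiator and navigation pathway, but do not enter them as predictors of dose. Keep total dose received as a descriptive figure by arm.

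The cost is wording in Table 3 and the analysis text. Visit completion and cycle initiator are already captured in the study database. The real drawback is sparse data: with roughly 36 and 20 patients having any ad hoc cycle under the illustrative rates, models must carry few predictors and within-arm results will be imprecise.
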